## 1. Introduction

The aim of this project is to evaluate in a single-center randomized clinical trial (RCT) whether the use of additional lidocaine could influence the NMB enhancement. Thus, this study's primary endpoint is the time at which spontaneous recovery of a train-of-four (TOF) ratio of 90% will be achieved (complete duration). The secondary endpoints are other NMB characteristics (onset time, duration 25, duration 95) and hemodynamic parameters.

This statistical analysis plan (SAP) will give more detailed descriptions of the endpoints in the study and the corresponding analyses.

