## 2. Study design

Sixty-four patients [American Society of Anesthesiologists (ASA) physical status I to II, aged 18 to 60 years] who will be scheduled for surgery (estimated surgical time greater than 90 min, with similar pain stimulus and no need for a continuous neuromuscular block during the surgical procedure) will be recruited. The exclusion criteria are patients with diseases or on medications known to interfere with neuromuscular transmission, hepatic or renal dysfunction, electrolyte abnormalities that can potentiate blockade, an allergy to the drugs used in the study, a body mass index  $<18$  or  $>29$  kg.m^-2, and those who are expected to have difficulties during mask ventilation or intubation, pregnant or breastfeeding.

The patients will be randomly and equally allocated into four groups (figure 1). The Computer-generated randomization will be stratified by gender to pursue equal distribution of intervention and control group for both male and female subjects, and the allocation concealed with sequentially numbered, sealed, opaque envelopes. The envelope's seal will be broken before the induction of general anesthesia by trained study personnel not involved in the data collection. Throughout the perioperative period, care providers, patients, and research team members will be blinded to the group assignments.

*Figure 1 Flowchart of screening and inclusion process*

[figure not shown]

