## 2.1 Sample size calculation

The primary outcome measure for the power calculation is the elapsed time for the TOF (T4/T1) recovery response to 90% of the original value after infusion of cisatracurium. For the sample size calculation, we considered a previous study showing magnesium sulfate prolonged the complete duration of rocuronium-induced NMB (*Acta Anaesthesiol Scand* 2010, 54(3):299-306). Having chosen a significance level of 5% and a power of 80%, we applied Satterthwaite's approximation (*Stat Med* 2001, 20(7):1089-1095). The result revealed N=14 patients per group, and we decided to randomized 16 patients in each group to allow for drop-outs.

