## 3. Aims and objectives

To investigate the effects of lidocaine associated with magnesium sulfate on the neuromuscular blockade promoted by cisatracurium and evaluate its possible hemodynamic repercussions.

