### 4.1 Primary outcome

Complete duration (T4/T1=90%): elapsed time for the TOF (T4/T1) recovery response to 90% of the original value after infusion of cisatracurium. This outcome measure will be presented in minutes.

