## 6. Analyses

All outcomes will be presented using descriptive statistics, normally distributed data by the mean and standard deviation (SD), and skewed distributions by the median and interquartile range (IQR). The Shapiro-Wilk test will be used to assess normality. The pharmacodynamic variables, clinical and demographic characteristics will be compared between the groups via the Kruskal-Wallis test, followed by Dunn's multiple comparison test or one-way ANOVA followed by the Tukey multiple comparison test, or the chi-square test, where appropriate. The area under the curve (AUC) will compare the study groups' hemodynamic responses. A p-value <0.05 will be considered statistically significant for all outcome variables. GraphPrisma version 8.3 will be used for all statistical analyses.

The subsections below will describe analyses in addition to the descriptive statistics.

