### 6.2 Secondary outcomes

Other characteristics of NMB and Hemodynamic changes will be analyzed using the same method as for the primary outcome, including usage of the baseline value for the actual factor as a covariate.

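### The 5% threshold applies to every outcome, with no error control across the eight secondary variables and no exploratory label

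*SAP*

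**What the plan says.** Section 6 of the SAP states: "A p-value <0.05 will be considered statistically significant for all outcome variables". Section 6.2 adds that "Other characteristics of NMB and Hemodynamic changes will be analyzed using the same method as for the primary outcome", with a baseline covariate.

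The single primary outcome, in section 4.1, is "Complete duration (T4/T1=90%): elapsed time for the TOF (T4/T1) recovery response to 90% of the original value after infusion of cisatracurium". Under section 4.2 and its hemodynamics part, the secondary outcomes are:

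- four NMB measures: onset time, clinical duration (25%), recovery index (25% to 75%) and total duration (95%);
- mean arterial pressure and heart rate in the induction period;
- mean arterial pressure and heart rate in the maintenance period.

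That makes six numbered items and eight variables. The introduction has a shorter list: "The secondary endpoints are other NMB characteristics (onset time, duration 25, duration 95) and hemodynamic parameters". It omits the recovery index.

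The only multiplicity procedures named are Tukey's test after one-way ANOVA and Dunn's test after Kruskal-Wallis, both in section 6. Nothing in the SAP orders the outcomes, splits the significance level, makes secondary tests depend on the primary, or labels the secondaries exploratory.

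**The concern.** A trial may leave its secondary outcomes unadjusted if it says that they are exploratory. This SAP does not say so. It prescribes the label of statistical significance for any outcome with a p-value below 0.05.

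The stated aim is broad. It covers the effect of the drug combination on NMB and also seeks to "evaluate its possible hemodynamic repercussions". Several secondary variables could therefore be read as answering it. An isolated result on, say, the recovery index or heart rate at induction would be reported as significant at 5%. The chance that some such result turns up among eight null variables is well above 5%. Tukey and Dunn do not help, because they protect the group comparisons within one outcome and not the search across outcomes.

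**Working it through.** **The plan's own figures.** The SAP states no error rate across outcomes, so there is none to reproduce. Its design figures are in section 2.1: "Having chosen a significance level of 5% and a power of 80%, we applied Satterthwaite's approximation", and "The result revealed N=14 patients per group, and we decided to randomized 16 patients in each group to allow for drop-outs". The 14 per group cannot be recomputed, because the effect size and standard deviations are only cited. This does not matter here, since the error rate across outcomes under the null does not depend on the sample size.

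**Inputs from the SAP.** Significance level 0.05 per outcome (section 6); four groups of 16 (sections 2 and 2.1); number of secondary variables k = 4 + 2 × 2 = 8 (section 4.2).

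**Assumptions not in the SAP.** No secondary variable truly differs between groups; data are normal; each variable gets one test (for the hemodynamic variables, one summary such as the area under the curve named in section 6); all pairs of outcomes share a common correlation, varied from 0 to 0.9.

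**Step 1: independent outcomes.** P(at least one false positive) = 1 − (1 − 0.05)^k.

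- k = 4 (NMB measures only): 1 − 0.95^4 = 0.1855
- k = 6 (the numbered items): 1 − 0.95^6 = 0.2649
- k = 7 (eight without the recovery index, as in the introduction): 1 − 0.95^7 = 0.3017
- k = 8: 1 − 0.95^8 = 0.3366

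**Step 2: correlated outcomes.** In 20,000 simulated null trials (four groups of 16, eight equally correlated normal outcomes), each outcome was tested at 0.05, by one-way ANOVA and separately by Tukey's test. The table gives the share of trials with at least one significant outcome.

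| Correlation | ANOVA | Tukey |
|---|---|---|
| 0 | 0.338 | 0.338 |
| 0.3 | 0.309 | 0.308 |
| 0.5 | 0.262 | 0.263 |
| 0.8 | 0.167 | 0.170 |
| 0.9 | 0.126 | 0.128 |

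The simulation standard error near 0.26 is √(0.26 × 0.74 / 20,000) ≈ 0.003. The first row agrees with the exact 0.3366. A separate large-sample calculation, with a 3-degree-of-freedom test in place of the ANOVA, gave 0.335, 0.305, 0.257 and 0.124 at correlations 0, 0.3, 0.5 and 0.9.

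The two columns are almost equal, which confirms that Tukey's test within each outcome leaves the rate across outcomes where it was. Dunn's test was not simulated, but it too acts only within one outcome.

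**Step 3: block structure.** Four outcomes with correlation 0.5 gave 0.162. If the NMB and hemodynamic blocks are independent of each other, with 0.5 within each, the rate is 1 − (1 − 0.162)^2 = 0.298; direct simulation gave 0.296.

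**Step 4: size relative to 5%.** 0.126 / 0.05 ≈ 2.5 and 0.338 / 0.05 ≈ 6.8.

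**The case against.** The SAP names one primary outcome, bases its sample size on that outcome alone, and calls the rest secondary. Testing secondaries at a nominal 5% and reading them as supportive is common practice, and a significance threshold can be taken as no more than a reporting convention. Much of this stands:

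- A reader might infer that secondary results have the same standing as the primary, or could rescue a trial whose primary fails. The SAP does not say that. It is silent on how secondary results may be used.
- A reader might also infer that the primary outcome's error rate is inflated. It is not: there is one primary outcome, and testing others does not change its 5%.
- No single percentage can be read from the SAP. It gives no correlations, and 26% for eight variables needs a correlation near 0.5 (by coincidence, it is also what six independent tests give). The three duration measures come from one T1 recovery course, so strong correlation among them is plausible and lowers the rate. The lowest figures, however, need high correlation across all eight variables, which nothing in the SAP supports.
- The null for all eight is a strong condition, since the sample size rests on an expected prolongation of blockade. If the four NMB measures truly differ, the four hemodynamic variables still give 16% at correlation 0.5 and 18.5% under independence.
- The number of hemodynamic tests is not settled. Section 6 names an area under the curve, while section 6.2 refers to the primary outcome's model with a baseline covariate. Eight assumes one test per variable and period; testing individual time points would raise the rate.

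What the objection does not remove is the wording of section 6. It calls every outcome below 0.05 statistically significant and adds neither an exploratory label nor an adjustment.

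**Conclusion.** The point holds for secondary claims only. Section 6 sets a significance rule for all outcomes without control across the eight secondary variables. If none of them truly differs and each is tested once, the chance of at least one false significant secondary is about 13% to 34%, depending on an assumed common correlation of 0.9 to 0. Even the low end is about two and a half times the nominal level.

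This is a modest defect that should be corrected because the correction is cheap. It does not threaten the primary analysis.

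**What to change.** Replace the significance sentence in section 6 with:

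> The 5% significance level applies to the primary outcome (complete duration). Secondary NMB and hemodynamic outcomes are exploratory and are reported as estimates with 95% confidence intervals and nominal p-values not adjusted across outcomes.

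There is no need to forbid the word 'significant'; the exploratory label and the statement that p-values are nominal are enough.

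If the sponsor wants formal secondary claims, apply Holm's procedure across the listed secondaries, tested only if the primary is significant. With eight variables the smallest p-value would be compared with 0.05 / 8 = 0.00625. This option needs a fixed list, so the introduction and section 4.2 should first agree on the recovery index, and each hemodynamic variable should have one named test.

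The cost is one sentence, with no new patients or data. The downside is that an isolated secondary p-value below 0.05 can no longer be presented as a confirmed effect.

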### 6.1 Primary outcome

The primary analysis will compare intervention groups on their mean change in NMB. The difference in time course to TOF=90% will be the dependent variable. Study subjects will be considered as random effects and treatment groups as fixed effects. The estimated difference in mean change from baseline and the corresponding 95 % confidence interval (CI) will be presented.

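### Section 6.1 does not say which of six group differences is primary, and the additional-lidocaine comparison is left as one unranked pair with about 60 to 68% power

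*SAP*

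**What the plan says.** The SAP's Introduction puts the question as "whether the use of additional lidocaine could influence the NMB enhancement". Section 3 words the aim as "To investigate the effects of lidocaine associated with magnesium sulfate on the neuromuscular blockade promoted by cisatracurium".

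Section 2 randomizes 64 patients equally to four groups. What each group receives is in Figure 1, which is not reproduced in the text at hand.

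Section 2.1 bases the sample size on a published effect of magnesium sulfate on rocuronium block: "Having chosen a significance level of 5% and a power of 80%, we applied Satterthwaite's approximation". It concludes: "The result revealed N=14 patients per group, and we decided to randomized 16 patients in each group to allow for drop-outs". It gives no mean difference or SD and does not say which two groups the calculation refers to.

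Section 6.1 states: "The primary analysis will compare intervention groups on their mean change in NMB". Treatment group is a fixed effect, and one estimated difference with a 95% CI is to be reported. No pair, reference group or contrast is named.

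Section 6 prescribes, for the pharmacodynamic variables, one-way ANOVA with Tukey or Kruskal-Wallis with Dunn, with a Shapiro-Wilk test to assess normality. No pair is singled out there either. It adds: "A p-value <0.05 will be considered statistically significant for all outcome variables".

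**The concern.** The Introduction asks a specific question, and specific questions are answered by specific contrasts. With four groups there are 4 × 3 / 2 = 6 pairwise differences, so a single estimated difference is undefined until the pair is named. Two things follow.

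- **Choice after the fact.** Nothing in section 6.1 prevents the headline difference from being picked once the six are known.
- **Power.** The only pairwise procedure in the SAP is an all-pairs one. The comparison that answers the Introduction then carries the multiplicity penalty of five comparisons that do not.

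There is also a risk of misreading. The sample size section shows that the sponsor expects magnesium to prolong the block. If magnesium differs between arms and the group comparison is taken as an overall test, that test can be significant because of magnesium while saying nothing about lidocaine.

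**Working it through.** **Inputs from the SAP.** Four equal groups, 64 patients (section 2); 5% significance, 80% power, N=14 per group raised to 16 (section 2.1). Check: 4 × 16 = 64, which agrees.

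**Assumptions.** The arms are control, lidocaine, magnesium and both; data are normal with equal SDs; tests are two-sided.

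**Step 1: the plan's own N.** N=14 cannot be reproduced, because no effect size is given. It can be back-solved if it was a two-group calculation. The normal approximation gives d = (1.960 + 0.842) × √(2/14) = 1.06 SD. The noncentral t with 26 df gives 80% power at n=14 when d = 1.10 SD. I use 1.10 and show other values. This is an inference from N, not an independent check of it.

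**Step 2: power for lidocaine plus magnesium versus magnesium alone.** The noncentrality is d × √(n/2), with df = 4(n − 1). The critical value is q(0.95; 4, df)/√2 under Tukey and t(0.975; df) for one prespecified contrast with pooled variance.

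| d (SD) | n per group | Noncentrality | Tukey critical value | Tukey power | Single-contrast critical value | Single-contrast power |
|---|---|---|---|---|---|---|
| 1.10 | 14 | 2.91 | 2.654 | 60% | 2.007 | 81% |
| 1.10 | 16 | 3.11 | 2.643 | 68% | 2.000 | 86% |
| 0.80 | 16 | 2.26 | 2.643 | 36% | 2.000 | 61% |

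For 80% power under Tukey at d = 1.10, about 20 per group are needed. The stated 80% is therefore met at 14 per group for a single contrast but not for an all-pairs procedure.

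**Step 3: an overall test when only magnesium acts.** Take group means of 0, 0, d, d, with a lidocaine effect of zero and n=16. The noncentrality is λ = n × Σ(μ − mean)² = 16 × 4 × (d/2)². At d = 1.10 this is 16 × 4 × 0.55² = 19.4. The F test has 3 and 60 df.

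| Magnesium effect (SD) | λ | Overall ANOVA significant |
|---|---|---|
| 0.5 | 4.0 | 34% |
| 0.8 | 10.2 | 74% |
| 1.1 | 19.4 | 96% |
| 1.5 | 36.0 | over 99% |

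At 1.1 SD, simulation gives at least one significant Tukey pair in 93% of such trials. The lidocaine-plus-magnesium versus magnesium pair itself is significant in about 1%.

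**The case against.** A reader might infer that the lidocaine question goes unanswered, or that a magnesium effect would automatically be reported as a positive primary result. The document supports neither.

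- Section 6 does test every pair with family-wise control. When lidocaine has no effect, the relevant Tukey pair is falsely significant in only about 1% of trials. The loss is in power and ranking, not an absent or misleading lidocaine test.
- Section 6.1 states no overall test, no gate and no rule that success rests on an overall p-value. The percentages in step 3 describe one possible reading. That the section leaves this open is part of the defect, but the reading should not be attributed to the sponsor.
- The arm contents are not visible, and 1.1 SD appears nowhere in the SAP. The magnesium evidence comes from rocuronium, whereas this trial uses cisatracurium, and nothing in the text supports giving lidocaine the same effect. At 0.8 SD a named contrast reaches only 61%, so naming it does not rescue a smaller effect.
- Section 3 can also be read as the combination against control, so the intended contrast is not beyond doubt.

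All four points stand. They limit the size of the claim. They do not supply the missing contrast, and the ambiguity between the Introduction and section 3 is a further reason to name it. One might also infer from the 0.05 rule that all other outcomes must be relabelled exploratory. Section 4.2 already lists the other pharmacodynamic measures and the hemodynamics as secondary, so that is a matter of preference and not part of this point.

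**Conclusion.** The point holds in this form: section 6.1 leaves its primary difference undefined among six, and the comparison the Introduction asks about has no rank above the others. That there is no named contrast depends on no assumption. The cost in power depends on the assumed arms and on the back-solved 1.1 SD: at that effect it is about 21 percentage points at 14 per group and 18 at 16. At 0.8 SD and 16 per group it is about 25 points. The possibility of a magnesium-driven positive result is conditional on magnesium differing between arms and on an overall test being read as primary. It then ranges from 34% to over 99% of trials across magnesium effects of 0.5 to 1.5 SD. This is worth correcting before unblinding, because following the plan as written weakens the answer to its own question and the remedy needs no more patients.

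**What to change.** In section 6.1:

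1. Name lidocaine plus magnesium versus magnesium alone, in complete duration, as the one primary contrast. Test it at two-sided 5% and report its 95% CI from the four-group model, with no overall test as a gate.
2. State one fixed method for this contrast in place of the Shapiro-Wilk switch to Dunn. Examples are log-transformed times in the four-group model, or a two-group rank test if a non-parametric route is kept.
3. Keep the other five pairs under Tukey or Dunn as secondary.

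The sponsor must first confirm that this contrast is the intended one, since section 3 also allows the combination against control. If another contrast is meant, it should be named in the same way.

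The cost is SAP wording only. The downside is that the other five pairs lose confirmatory status.

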### 5.2 Subgroups

Not applicable

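### Randomisation is stratified by gender but no planned analysis includes it; if gender predicts the outcome, intervals will be too wide and tests conservative

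*SAP*

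**What the plan says.** Section 2 of the SAP describes the design: "The patients will be randomly and equally allocated into four groups". On stratification it says: "The Computer-generated randomization will be stratified by gender to pursue equal distribution of intervention and control group for both male and female subjects".

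The analysis sections take no account of that stratification:

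- **Section 6** names the group comparisons as Kruskal-Wallis, "followed by Dunn's multiple comparison test or one-way ANOVA followed by the Tukey multiple comparison test, or the chi-square test, where appropriate". None is stratified or adjusted. Gender could appear there as a demographic characteristic compared between groups, but that does not put it into the analysis of an outcome.
- **Section 6.1** gives the primary model: "Study subjects will be considered as random effects and treatment groups as fixed effects". The result to be reported is an estimated mean difference with a 95% confidence interval.
- **Section 6.2** uses the same method for the secondary outcomes, "including usage of the baseline value for the actual factor as a covariate". That covariate is the outcome's own starting value, not gender.
- **Section 5.2**, on subgroups, says "Not applicable", so gender does not enter by that route.

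The SAP gives no reason for leaving the stratification factor out.

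**The concern.** Stratified randomisation makes the groups alike in gender. Whatever gender contributes to the outcome then largely cancels from each between-group difference. A model without a gender term does not register this, because the male-female difference remains in the residual variance from which the standard error is computed. If gender matters for the outcome, the computed standard error exceeds the true one. Intervals then cover more than 95%, tests reject less often than 5% under the null, and power is lost.

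The random subject effect does not stand in for gender. The primary outcome is one time per patient (Section 4.1), so a subject effect cannot be separated from residual error.

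At stake is precision in a trial whose calculation in Section 2.1 gave 14 patients per group, with 16 randomised to allow for drop-outs.

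**Working it through.** **Inputs from the SAP.** Four equal groups of 16, 64 patients in all, 5% significance and 80% power (Sections 2 and 2.1).

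**Assumptions.** Tests are two-sided. Gender is split 8/8 in every group. Within-gender SD is 1. The gender gap *g*, in within-gender SDs, runs from 0 to 1.0. The SAP gives none of these.

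**The plan's own figure.** The 14 per group cannot be reproduced, because Section 2.1 states neither a mean difference nor an SD. Solved backwards with the normal formula, it implies a treatment effect of (1.960 + 0.842) × √(2/14) = 1.059 SD. That value is used below only as a scale for power.

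**Formulas.** With an even split, gender adds variance g²/4, so

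- share of variance due to gender: R² = (g²/4) / (1 + g²/4)
- interval width relative to a model with gender: 1/√(1−R²)
- equivalent extra patients: 1/(1−R²) − 1
- type I error of one unadjusted pairwise test: P(|t₆₀| > 2.000/√(1−R²))
- type I error of the global F-test: P(F₃,₆₀ > 2.758/(1−R²))

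The last two are approximations, so they are set beside simulation (20,000 or more trials per setting; at 20,000, the standard error of a 5% rate is √(0.05 × 0.95/20,000) = 0.15 percentage points).

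Example at g = 0.5: g²/4 = 0.0625; R² = 0.0625/1.0625 = 5.9%; width 1/√0.941 = 1.031; critical value 2.000/0.970 = 2.062, giving 4.4%.

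| Gender gap (SD) | R² | Interval wider by | Extra patients | Pairwise type I error: formula / simulated | F-test type I error: formula / simulated |
|---|---|---|---|---|---|
| 0 | 0% | 0% | 0% | 5.0% / 5.1% | 5.0% / 5.0% |
| 0.25 | 1.5% | 0.8% | 1.6% | 4.8% / 4.8% | 4.7% / 5.0% |
| 0.5 | 5.9% | 3.1% | 6% | 4.4% / 4.2% | 4.1% / 3.9% |
| 0.67 | 10% | 5.4% | 11% | 3.9% / 4.0% | 3.5% / 3.3% |
| 1.0 | 20% | 11.8% | 25% | 2.9% / 3.0% | 2.2% / 2.1% |

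The t distribution must be used throughout. Pairing the critical value 2.00 with a normal tail gives 4.55% at R² = 0, which shows conservatism where there is none.

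**With a gender term.** In simulation the F-test returns to 4.8% to 5.2%, and pairwise coverage to 94.7% to 95.2%, at every gap tried. Kruskal-Wallis without gender behaves like the ANOVA: 4.2% at 0.5 SD and 2.1% at 1.0 SD.

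**Power.** With one group shifted by 1.059 SD, F-test power is:

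| Gender gap (SD) | Without gender | With gender |
|---|---|---|
| 0 | 85.6% | 85.5% |
| 0.5 | 83.9% | 86.0% |
| 0.8 | 79.9% | 86.1% |
| 1.0 | 75.8% | 85.7% |

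**The case against.** The strongest reply is that the harm may be nil. The SAP holds no evidence that gender affects time to TOF 90%. Up to a gap of 0.25 SD the planned tests run at about 5% with intervals less than 1% wider. A gap of 1.0 SD would make gender almost as strong as the 1.059 SD treatment effect implied by the sample size. This stands, and it is why the range above starts at zero.

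A reader might infer from the stratification that the sponsor judged gender to be prognostic. The text does not say so; the reason it gives is equal distribution of the groups among men and women. A reader might also infer that the intervals are certainly too wide. They are too wide only if gender is prognostic and balanced. Nor is the planned analysis invalid: the error is on the cautious side and the estimates are unbiased.

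Balance is itself assumed. The SAP gives neither block sizes nor the expected gender mix, and the protocol may hold both. An uneven mix weakens the effect: with a 25/75 split and a 1.0 SD gap, R² = 0.1875/1.1875 = 15.8% rather than 20%.

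The reply does not remove the omission. Sections 6 to 6.2 specify the tests and model terms, and the stratification factor is not among them.

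**Conclusion.** The point holds conditionally. It is certain that the analyses do not reflect the stratified design. The consequence depends on how strongly gender predicts the outcome:

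- **No gender effect:** nothing is lost.
- **0.5 SD:** a small loss, with intervals about 3% wider and type I error about 4.3% for one pair and about 4% for the F-test.
- **0.67 SD:** intervals about 5% wider, with type I error about 3.9% and 3.3% to 3.5%.
- **1.0 SD:** intervals about 12% wider, with type I error about 2.9% and about 2%, and roughly ten points of power lost in the scenario examined.

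These figures rest on an 8/8 gender split in each group, equal variances and two-sided tests. The point should be acted on because the correction costs almost nothing, not because the planned results would mislead.

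**What to change.** In Section 6.1, add gender as a fixed factor beside treatment group. In Section 6.2, add it beside the baseline covariate. In Section 6, where a rank test is kept, name a gender-stratified version (van Elteren type for pairwise comparisons). If the sponsor prefers to leave gender out, the SAP should say why.

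The cost is SAP wording and one degree of freedom: residual degrees of freedom go from 60 to 59 with 64 patients, and power at zero gender effect is practically unchanged. Nothing changes in trial conduct or data collection. The sponsor should confirm that the software named in Section 6 can run the adjusted model and the stratified rank test. The change should be made before unblinding, so that the choice between adjusted and unadjusted results is not made after seeing them.

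### Section 6.1 mis-specifies the primary analysis: complete duration is one time per patient with no baseline, so a change from baseline is undefined and a random subject effect cannot be identified

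*SAP*

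**What the plan says.** Section 4.1 defines the primary outcome as "elapsed time for the TOF (T4/T1) recovery response to 90% of the original value after infusion of cisatracurium" and adds: "This outcome measure will be presented in minutes".

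Section 6.1 then describes the analysis in four steps:
- the comparison: "The primary analysis will compare intervention groups on their mean change in NMB"
- the response: "The difference in time course to TOF=90% will be the dependent variable"
- the model: "Study subjects will be considered as random effects and treatment groups as fixed effects"
- the reported result: "The estimated difference in mean change from baseline and the corresponding 95 % confidence interval (CI) will be presented"

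Section 6.2 applies this method to the other neuromuscular blockade (NMB) characteristics and to the hemodynamic outcomes, "including usage of the baseline value for the actual factor as a covariate".

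Section 6 contains a separate instruction: "The pharmacodynamic variables, clinical and demographic characteristics will be compared between the groups via the Kruskal-Wallis test", with Dunn's test to follow, or else by one-way ANOVA with Tukey's test. Normality is assessed by Shapiro-Wilk. Hemodynamic responses are to be compared by area under the curve (AUC).

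**The concern.** The model in section 6.1 is written for an outcome measured before and after treatment, or repeatedly. Complete duration is neither. Three things follow.

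- The quantity promised as the primary result is not defined for this outcome.
- The random subject effect has no information to estimate it. Software may still return output, but the standard errors and confidence intervals may be wrong.
- Whoever repairs the model has to decide what to drop, and section 6 offers both a mean-based and a rank-based test of the same variable with no statement of which one decides.

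If the text stays as it is, these choices may be made with the data in view. An analysis plan is meant to prevent that, most of all for the primary outcome.

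**Working it through.** **Inputs from the SAP.** Four equal groups (section 2); 14 patients per group calculated and 16 randomized (section 2.1), so 4 x 16 = 64 patients. Outcome definitions are in sections 4.1 and 4.2, the models in sections 6, 6.1 and 6.2.

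**The plan's own figure.** The 14 per group cannot be reproduced, because the SAP gives neither a difference nor a standard deviation. Solved backwards under an assumed two-sided 5% level and 80% power, d = sqrt(2/14) x (1.960 + 0.842) = 1.06 standard deviations by the normal formula, or 1.10 with the t distribution. An assumed one-sided 5% level gives 0.94 or 0.97. The step from 14 to 16 matches 12.5% drop-out: 14/(1 - 0.125) = 16. Nothing below depends on these figures.

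**Step 1: does each outcome have a baseline?**

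| Outcome | Values per patient | Pre-drug value of the same quantity | What 6.1 or 6.2 asks for |
|---|---|---|---|
| Complete duration (primary) | 1 | none | change from baseline, random subject |
| Onset time | 1 | none | same method plus baseline covariate |
| Duration 25% | 1 | none | same method plus baseline covariate |
| Recovery index | 1 | none | same method plus baseline covariate |
| Duration 95% | 1 | none | same method plus baseline covariate |
| MAP, HR | several | yes | same method plus baseline covariate |

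The original value named in section 4.1 is a reference twitch response that fixes when the 90% endpoint is reached. It is not a baseline time in minutes. The change from baseline is therefore undefined for the primary outcome, and the covariate is undefined for 4 of the 4 secondary NMB measures.

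**Step 2: is the random subject effect identifiable?** For patient i in group j, the model is y_ij = mu_j + u_ij + e_ij, where u has variance s_u^2 and e has variance s_e^2. With one value per patient, Var(y_ij) = s_u^2 + s_e^2 and all covariances are zero. Only the sum enters the likelihood.

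This was checked on simulated data: 4 groups of 16, true means 60, 65, 70 and 75, SD 10. These values are assumed for illustration and are not taken from the SAP. With the total variance held at 100 and 0, 25, 50, 75 or 100% of it assigned to subjects, the REML log-likelihood was -166.620676 every time and the group means did not move.

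**Step 3: what does a literal fit return?** On the same simulated data:

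| | Mixed model, random subject | One-way ANOVA |
|---|---|---|
| Variance | 38.2 subject, 38.2 residual | 76.4 residual |
| SE of the three contrasts with group 1 | 2.29, 2.12, 2.16 | 3.09 each |
| SE of intercept | 0.13 | 2.19 |

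The equal split is arbitrary, and the program warned that the Hessian was not positive definite. The total variance, 38.2 + 38.2 = 76.4, is sound: sqrt(76.4 x 2/16) = 3.09, the ANOVA standard error. The standard errors printed by the mixed model do not agree with it. They are 68% to 74% of the correct value (2.12/3.09 = 0.68; 2.29/3.09 = 0.74), so intervals built on them are too narrow.

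**Step 4: what remains estimable?** Without the baseline and subject terms, the model has four group means and one residual variance. That is one-way ANOVA on minutes, with 64 - 4 = 60 residual degrees of freedom at full enrollment. Four groups give 4 x 3/2 = 6 pairwise differences, and section 6.1 names none of them.

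**Step 5: section 6 beside section 6.1.** Section 4.2 introduces its list as the other pharmacodynamic measures, so complete duration is itself one of the pharmacodynamic variables tested in section 6. Section 6 says its subsections add to the descriptive statistics; it does not say they replace its tests. On the ANOVA branch, section 6 and the corrected section 6.1 agree. On the Kruskal-Wallis/Dunn branch they do not, because rank tests give no mean difference with a confidence interval.

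**The case against.** The strongest reply is that the defect is one of wording. Group mean differences are estimable, the model reduces to one-way ANOVA, and section 6 already names that test. Only section 6.1 carries the label of primary analysis, so a hierarchy is implied. The branch in section 6 is tied to a normality check and is not wholly free. All of this is correct, and it rules out several stronger conclusions a reader might draw.

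- *That the primary comparison cannot be carried out at all.* It can, once two terms are removed.
- *That the plan holds two incompatible primary analyses.* Section 6 never calls its tests primary, and the conflict is confined to the Kruskal-Wallis/Dunn branch.
- *That the baseline covariate is wrong for all five NMB times.* Section 6.2 sets it for the secondary outcomes only. The primary outcome has a different fault, the change from baseline.
- *That the model must be replaced after the data are seen.* It can be corrected beforehand. Post-hoc choice is a risk only if the text is left alone.

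What the reply does not meet is that the SAP nowhere tells the analyst to drop either term, and no text says which result decides. Nor is the baseline language a mere slip: section 6.2 repeats it as a covariate for times that have no baseline. The model may suit the repeated MAP and HR readings, but that does not make it suitable for the primary outcome.

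**Conclusion.** Section 6.1 is wrong as written and should be corrected before data are seen. The primary estimate is undefined as a change from baseline, and the subject variance is not identifiable. Section 6.2 extends the method to all four secondary NMB times, and the standing of the section 6 tests is unsettled on the rank branch.

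The identifiability result needs no assumption beyond one value per patient, which sections 4.1 and 4.2 establish. The count of 64 values assumes no drop-outs; fewer patients would not change the argument. The size of the standard-error distortion comes from one simulated data set and one program. It shows that a literal fit can mislead, and does not predict what the package named in section 6 would print. The sample size is not affected. The conclusion rests on the SAP alone, since the protocol is not at hand.

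**What to change.** **Section 6.1.** Restate it as a linear model of complete duration in minutes with treatment group as a fixed factor, no baseline term and no subject random effect. Gender, the randomization stratum, may be added as a fixed factor; this is optional and separate from the defect. Report between-group differences in mean duration with 95% CIs for named pairwise contrasts, with multiplicity control, for example Tukey across all six pairs. State that this replaces the choice between ANOVA and Kruskal-Wallis in section 6 for the primary outcome, and that Kruskal-Wallis/Dunn is a sensitivity analysis only.

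**Section 6.2, NMB times.** Use the same model, without a baseline covariate, for onset time, duration 25%, recovery index and duration 95%.

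**Section 6.2, MAP and HR.** Confine the baseline covariate to these outcomes and say which pre-drug reading supplies it. State whether they are analyzed by a repeated-measures model with a subject random effect, or by one AUC per patient without one. A single AUC per patient would bring back the identifiability problem if the random effect were kept. Either choice must agree with the AUC statement in section 6.

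**Cost.** SAP wording only. No change to sample size, data collection or conduct.
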